### 2.9. Primary outcomes

The primary outcome will be the change in platelet aggregation rate of elbow venous blood for platelet adhesion properties at baseline, 14^th^ day and 30^th^ day of treatment; Moreover, the serum TLR4, MyD88, NF-*κ*B, COX-2, IL-6, CRP, TXB2 level for AR improvement based on the TLR4/MyD88/NF-*κ*B signaling pathway would be also detected at above-mentioned 3 time points.

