## 1. Introduction

Despite the rapid development of medicine, stroke is still a major cause of death worldwide.^[1]^ Platelet activation still plays an important physio-pathological role in cerebrovascular thromboembolism events. Therefore, antiplatelet drugs, especially aspirin, play a vital role in the secondary stroke prevention.^[2]^ Since the 1990s, it has been found that about 5% to 60% patients still exist stroke recurrence when taking aspirin orally in clinical practice. This phenomenon has been called “aspirin resistance (AR)^.^”^[3]^ Currently, AR is divided into clinical AR and laboratory AR. Clinical AR refers to that it failures to inhibit thromboxane A2 (TXA2) production and TXA2- dependent platelet aggregation after regular aspirin administration. Laboratory AR is defined as arachidonic acid -induced mean platelet aggregation rate ≥ 20% and adenosine diphosphate -induced mean platelet aggregation rate ≥ 70%. Those who meet 1 of above 2 criteria are aspirin semi-resistance (ASR) ones.^[4]^ It has been reported that AR may increase the risk of recurrent cerebrovascular events by 2 times and the risk of death by 3.5 times,^[5]^ which brings heavy economic burden to the society and families.

Mechanisms of AR are multiple and complex, including clinical, genetic, pharmaco- logical, and biological factors.^[4]^ How to enhance bioavailability to overcome AR, there is no unified standards. It may mainly increase dose and frequency of drug, or combine with other antiplatelet drugs, which are lack of effective medical evidence,^[6]^ and increase risk of hemorrhage. Therefore, it’s urgent to find a safe and effective partial substitute of aspirin for AR individuals.

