### 2.3. Study population

#### 2.3.1.
*Inclusion criteria*.

1.Subjects, diagnosed with ischemic stroke, according to the *International Classification of Diseases (ICD-11, 8B11*),^[12]^ and *Chinese Guidelines for Diagnosis and Treatment of Acute Ischemic Stroke 2018*;^[13]^

2. Subjects, diagnosed with aspirin semi-resistance, according to 0.5 mmol/L arachidonic acid-induced mean platelet aggregation rate ≥ 20%, or 10*μ*mol/L adenosine diphosphate-induced mean platelet aggregation rate ≥ 70%;^[4,14]^

3. Subjects, aged between 45 and 65 years old, male or female;

4. Subjects, predicted in the low-risk profile of recurrent stroke, Essen stroke risk scores ≤ 3 points;^[15]^

5. Only taking single antiplatelet drug, not overlapping the use of activating blood and removing stasis herbs medicine;

6.Sign the informed consent forms.

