### 2.11. Estimation of sample size

The study is powered for the primary outcome measure of platelet aggregation rate. The number of patients required for the study was computed a priori with software PASS 15.0.1, NCSS, LLC, America. The sample size calculation was based on the results of preliminary small sample pilot trial by our team, which showed a decrease of-14% in platelet aggregation rate in the exercise group compared with control group (autocorrelation coefficient 0.7, 3 time points). A 1-sided 0.05 level of significance and a sample size of 96 participants (48 per group) provided 80% statistical power to demonstrate this difference in platelet aggregation rate. To accommodate for a 10% attrition rate, we will recruit a total of 106 participants (53 per group) (PASS 15.0.1, 2-way repeated measures Anova; allocation ration = 1).

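### The primary outcome and the 14% planning difference do not say which of the two agonist-specific platelet aggregation rates used for entry is meant, so two primary variables stay open and the 80% power is tied to neither

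*Protocol article*

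**What the plan says.** Eligibility in section 2.3.1 rests on two assays with different cut-offs, joined by an or: "0.5 mmol/L arachidonic acid-induced mean platelet aggregation rate ≥ 20" per cent, or "adenosine diphosphate-induced mean platelet aggregation rate ≥ 70" per cent. The Introduction reserves laboratory aspirin resistance for patients meeting both and adds: "Those who meet 1 of above 2 criteria are aspirin semi-resistance (ASR) ones".

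After that the agonist disappears. Section 2.9 reads "The primary outcome will be the change in platelet aggregation rate of elbow venous blood for platelet adhesion properties". Section 2.11 says "The study is powered for the primary outcome measure of platelet aggregation rate" and takes its planning difference from the team's pilot, "which showed a decrease of-14% in platelet aggregation rate in the exercise group compared with control group". Section 2.13.1 analyses platelet aggregation rate at baseline, day 14 and day 30 by two-way repeated measures ANOVA and reads the group effect as the treatment comparison. None of these sections names AA or ADP, gives a rule for combining them, or says whether the 14% is in percentage points or relative.

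**The concern.** The article separates the two rates carefully, with concentrations and cut-offs, when it defines who may enter. It then treats them as one quantity when it defines what is tested. This has two consequences.

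First, either rate could later be reported as the primary outcome, or both could be tested at the full 0.05. Nothing in the text prevents the choice from following the data.

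Second, an either/or entry rule means that, on whichever rate is analysed, some patients may have qualified only on the other. Their value on the analysed rate was below the resistance cut-off at entry. If they can show less of the planned effect, the average difference in the trial is smaller than the 14% used for planning, unless that 14% already reflects such a mixture.

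**Working it through.** **Inputs from the article.** AA cut-off 20%, ADP cut-off 70%, either one sufficient (2.3.1). Planning difference 14%, correlation 0.7, three time points, one-sided 0.05, 80% power, 48 per group (2.11). Not given: the SD, the agonist and scale of the 14%, the pilot's entry rule, and the expected shares qualifying on AA only, ADP only or both.

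**1. The plan's own figure.** Without an SD, 96 participants cannot be derived forward. Working backward, if the 14% means percentage points and the test is the group effect over three time points, the variance factor is (1 + 2 × 0.7)/3 = 0.80. One-sided 0.05 with 80% power needs a standardised distance of 1.645 + 0.842 = 2.486 (from unrounded values). The detectable effect is 2.486 × √(2 × 0.80/48) = 0.454 SD, so the implied SD is 14/0.454 ≈ 30.8 points. For a single time point it would be 27.6. This neither confirms nor refutes 96, and it does not reveal which rate was used.

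**2. Two open primary variables.** If both rates are tested at 0.05, or the better one is reported, the chance of at least one false positive is at most 1 − 0.95² = 0.0975 for independent tests. Both rates are measured in the same patients, so positive correlation is likely and the figure would then lie between 5% and 9.8%.

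**3. Room to show the planned fall.**
- Analysed rate AA: a patient who entered on ADP alone starts below 20%. A fall of 14 points would remove most of that, and is impossible from a baseline below 14%. If the 14% is relative, the problem goes away: 14% of an AA rate of 18% is about 2.5 points.
- Analysed rate ADP: a patient who entered on AA alone starts somewhere below 70%, which can leave tens of points to fall. No floor follows.

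**4. What that could do to power.** Let f be the share who did not qualify on the analysed rate and r the fraction of the full effect they can show. Both are assumptions. Suppose also that the 14% came from patients who all qualified on the analysed rate. The average effect is then multiplied by k = (1 − f) + f·r, and power at one-sided 0.05 with 48 per group is Φ(2.486·k − 1.645).

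| f | r = 0 | r = 0.5 | r = 0.75 | r = 1 |
|---|---|---|---|---|
| 0.2 | 63.5% | 72.3% | 76.3% | 80% |
| 0.3 | 53.8% | 68.0% | 74.4% | 80% |
| 0.5 | 34.4% | 58.7% | 70.2% | 80% |

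For f = 0.3 and r = 0.5, for example, k = 0.7 + 0.15 = 0.85 and Φ(2.113 − 1.645) = 0.68. Restoring 80% at f = 0.3 takes 48/k² per group: 98 for r = 0, 67 for r = 0.5, 57 for r = 0.75 and 48 for r = 1.

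**5. The exception.** If the pilot used the same either/or entry rule and the same rate, its 14% is already the average over the mixture, and power is 80% whatever f and r are.

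**The case against.** A condensed article may leave assay detail to the full protocol, version V1.0, which is not shown. That would excuse a missing laboratory method. It is a weaker defence here, because the article does give agonists and concentrations for eligibility and drops them only for the endpoint, the planning difference and the analysis. Which of two variables is primary is a basic part of the design.

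It can also be said that nothing in the article announces a choice between the rates, that both might be analysed, and that two measures of platelet aggregation are unlikely to be independent. All of that stands. It makes 9.8% an upper bound, not an estimate.

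The strongest objection concerns power. A reader might infer that patients have little room to improve on either rate and that power is therefore below 80%. The article does not support this. The floor argument works only for AA, and only if the 14% is in points. A value below a resistance cut-off can still fall. The 14% comes from the team's own pilot, whose entry rule is not given and may have been the same. Assuming no response at all from patients who qualified on the other rate is the extreme case. On the other side, the article does not say that the pilot shared the rate or the entry rule, and it attributes the 14% to an exercise group, which is not an arm of this trial. The match cannot be taken for granted either.

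**Conclusion.** The point holds as a badly fixed primary endpoint. Entry uses two rates with different cut-offs, while the outcome, the planning difference and the analysis refer to one unnamed rate. That leaves two candidate primary variables, with a type I error above 5% and at most 9.8% if the better one is chosen or both are tested at 0.05.

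The effect on power is a possibility, not a demonstrated loss. With 30% of patients not qualifying on the analysed rate, power is 54%, 68% or 80% as they show none, half or all of the effect. These figures rest on assumed shares and responses, and on a pilot population that differs from the trial's. If it does not differ, power stays at 80%.

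A reader might arrive at lower figures by starting from about 70%. That starting point comes from sizing the trial at one-sided 0.05 (2.11) and testing at two-sided 0.05 (2.13). It is a separate matter and should not be charged to this one.

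**What to change.** - In 2.9, name one agonist-specific rate at day 30 as the primary outcome, namely the one that gave the pilot's 14%, and make the other secondary.
- In 2.13 and 2.13.1, compare the groups on that rate with adjustment for its baseline value and for the qualifying criterion (AA only, ADP only, both). This should replace a group effect over three time points, which averages in a measurement taken before treatment.
- In 2.11, say whether the 14% is in points or relative. Give its SD for the named rate in a population entered by the same either/or rule. If the pilot population differed, state the expected share in each qualifying class and restate the average difference and the power.

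The cost is wording in three sections. The entry data and the baseline rate are already collected, and eligibility and treatment are untouched. The restated effect or power may look less favourable than 80%.

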### 2.10. Secondary outcomes

The secondary outcome will be the change of coagulation function for platelet assay and hemorrhage risk of stroke patients at 0 day, 14^th^ day and 30^th^ day of treatment. In addition, changes in liver and kidney function will be also tested for the medication safety in patients pre-and post-treatment. Their blood glucose, blood lipids, blood pressure, AEs and others will be tracked in patients diary during period. All the dropouts and causes will be documented in case report forms.

### 2.11. Estimation of sample size

The study is powered for the primary outcome measure of platelet aggregation rate. The number of patients required for the study was computed a priori with software PASS 15.0.1, NCSS, LLC, America. The sample size calculation was based on the results of preliminary small sample pilot trial by our team, which showed a decrease of-14% in platelet aggregation rate in the exercise group compared with control group (autocorrelation coefficient 0.7, 3 time points). A 1-sided 0.05 level of significance and a sample size of 96 participants (48 per group) provided 80% statistical power to demonstrate this difference in platelet aggregation rate. To accommodate for a 10% attrition rate, we will recruit a total of 106 participants (53 per group) (PASS 15.0.1, 2-way repeated measures Anova; allocation ration = 1).

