### 2.5. *Study group*

106 participants who meet above-mentioned criteria with signed informed consents will be selected. The subjects will be randomly divided into 2 groups in a 1:1 ratio, namely the experimental group and control group, 53 cases in each group.

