### 2.13. Statistical analysis

Data analysis will be based on the full analysis set and per-protocol set in the light of data missingness (last-observation-carried-forward [LOCF] method) and robustness of our analytical results. All data will be analyzed using IBM SPSS Statistics 21.0 (v21.0, IBM Corp., Armonk, NY). Descriptive statistics will be performed with means ± standard deviations or median [interquartile range]. Baseline characteristics of patients will be summarized by groups and compared with Chi-square for categorical variables, and Student’s independent *t* test or nonparametric Mann-Whitney U test for the continuous variables. Primary and secondary outcomes are applicable to 2-way repeated measures Anova, and Post Hoc test will be for multiple comparisons between groups and time-points. If there is a violation of distribution assumption, appropriate transformation will be used. A *P* value < 2- sided 0.05 will be considered as significant.

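### The only effect estimate behind the sample size is credited to an exercise group that this trial does not have, its meaning is left open, and the 80% power is 1-sided while the analysis is 2-sided

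*Protocol article*

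**What the plan says.** Section 2.11 (Estimation of sample size) powers the trial on platelet aggregation rate. On the source of the effect it says "The sample size calculation was based on the results of preliminary small sample pilot trial by our team", and that this pilot "showed a decrease of-14% in platelet aggregation rate in the exercise group compared with control group". The other inputs are "autocorrelation coefficient 0.7, 3 time points", the test ("2-way repeated measures Anova; allocation ration = 1") and the result: "A 1-sided 0.05 level of significance and a sample size of 96 participants (48 per group) provided 80% statistical power". Allowing for 10% attrition, 106 are to be recruited. No SD or standardised effect is given.

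Section 2.5 describes the arms as "namely the experimental group and control group, 53 cases in each group". Section 2.7 defines the experimental arm as conventional treatments plus Panax notoginseng and the control arm as conventional treatments alone.

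Section 2.13 (Statistical analysis) sets the significance rule: a P "value < 2- sided 0.05 will be considered as significant".

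**The concern.** A power statement is only as good as the effect it rests on. Here one effect is cited, and it is credited to an arm that appears nowhere else in the text. If the 14% came from another intervention, the 80% claim has no basis for Panax notoginseng. If the word is a slip, the reader still does not know what difference was planned for. The outcome is itself a percentage, so 14% may be points or a relative change, and section 2.3.1 uses two aggregation assays with very different cut-offs (arachidonic acid at least 20%, ADP at least 70%).

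The stated power also belongs to a 1-sided test that the analysis section does not plan. This can be sized without knowing anything about the pilot.

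**Working it through.** **Arm labels.** The abstract and sections 2.1, 2.5, 2.7 and 2.12 all describe two arms, conventional treatments with or without Panax notoginseng. Exercise appears only in section 2.11. The Introduction says that aspirin plus Panax notoginseng powder did better than aspirin alone in an analysis of current cases. It gives no figure there and does not link that analysis to the pilot.

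**Trying to reproduce 48 per group.** Inputs from section 2.11: 1-sided alpha 0.05 (z = 1.645), power 80% (z = 0.842), correlation 0.7, three time points, 1:1 allocation. For a comparison of two means,

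n per group = 2 × (1.645 + 0.842)² × f × (SD/d)²,

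where d is the difference and f is the variance factor of the contrast:

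- single time point: f = 1
- mean of three visits, compound symmetry: f = (1 + 2 × 0.7)/3 = 0.80
- mean of three visits, AR(1): f = [3 + 2 × (2 × 0.7 + 0.7²)]/9 = 6.78/9 = 0.753

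Without an SD, n cannot be computed. Solving backwards with n = 48, d/SD = 2.487 × √(2f/48):

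| Contrast (assumed) | d/SD, 1-sided 0.05 | SD implied if 14% means 14 points |
|---|---|---|
| Single time point | 0.508 | 27.6 |
| Mean of three, compound symmetry | 0.454 | 30.8 |
| Mean of three, AR(1) | 0.441 | 31.8 |

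With the exact t distribution the last two d/SD values are 0.457 and 0.444. Section 2.13.1 interprets the group effect, which points to the mean of three visits, but section 2.11 does not name the powered term. The stated 48 thus fixes a standardised difference of about 0.44 to 0.46 SD, or about 0.51 SD for a single time point. It does not fix a difference in points. For a 14-point difference under AR(1), the formula gives 20 per group at SD 20, 30 at SD 25, 43 at SD 30 and 59 at SD 35.

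**Sidedness.** This step needs neither the SD nor the meaning of 14%. If 48 per group has 80% power at 1-sided 0.05, the expected test statistic is 1.645 + 0.842 = 2.487, whatever f is. At 2-sided 0.05 the critical value is 1.960, so

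power = Φ(2.487 − 1.960) = Φ(0.527) ≈ 0.70.

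For 80% power, n per group = 48 × [(1.960 + 0.842)/2.487]² = 60.9, that is 61.

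**Detectable difference at 2-sided 0.05 with 48 per group**, 2.802 × √(2f/48): 0.57 SD for a single time point; 0.51 SD (compound symmetry) or 0.50 SD (AR(1)) for the mean of three visits.

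**Attrition.** 96 × 1.10 = 105.6, which rounds up to 106; dividing by 0.90 gives 106.7, or 107. The difference is one patient and is not part of this point.

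**The case against.** The strongest defence is that one word is wrong. The sentence describes the team's own pilot, on platelet aggregation rate, against a control group. Experimental group is the document's usual term, and the Introduction reports a favourable comparison for this product. A slip for experimental is therefore plausible. This stands, and it rules out the inference that the effect is known to come from an exercise trial. It does not settle the matter, because nothing in section 2.11 names the pilot's intervention or population.

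A missing SD or pilot size can also be put down to journal condensation. That stands too: their absence is not the fault here, and it matters only because it leaves the reader no other way to identify the planned effect.

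Two stronger readings are tempting and are not supported:

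- A reader might infer that 14 points is impossible, because values confined to 70–100% have an SD of at most 15 and the implied SD is about 28 to 32. But entry is by arachidonic acid or ADP, so patients who qualify on the first can have ADP values below 70%. Arachidonic acid values from 20% to 100% allow an SD up to 40. The visits on treatment are not bound by the entry cut-offs.
- A reader might set 14 points against 14% of the entry cut-offs (0.14 × 70 = 9.8; 0.14 × 20 = 2.8) and claim a five-fold range in the planned difference. That mixes two assays and takes each at its entry minimum, so it does not measure the real uncertainty.

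Finally, the 1-sided label could itself be the error. If the calculation was in fact run at 2-sided 0.05, the 80% could stand and only the label would change. The document gives no sign of this.

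**Conclusion.** The concern holds in a limited form. Section 2.11 names an arm that the trial does not have as the source of its only effect estimate, and leaves open both the assay and whether 14% is absolute or relative. The document does not show whether this is a wording slip or text from elsewhere, so it does not establish that the planned effect is unrelated to Panax notoginseng. Nor does it show an arithmetic error in the 48 per group, which can be neither confirmed nor refuted as printed.

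The part that can be sized is the power. It is about 70% rather than 80% under the planned 2-sided test, assuming that the calculation was run 1-sided as stated and that 48 per group are evaluable. The normal approximation is used; the result does not depend on the correlation structure or on what 14% means. The implied standardised difference does depend on the assumed contrast.

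**What to change.** Check the pilot record and rewrite section 2.11 accordingly.

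- If the pilot tested Panax notoginseng: correct the arm label; state the assay, whether 14% is percentage points or a relative fall, and the SD; name the powered contrast; and restate the power at 2-sided 0.05. That is about 70% with 48 per group if the standardised difference is the one implied by the stated 1-sided 80%. Keeping 80% would need about 61 evaluable per group.
- If it tested another intervention: withdraw the 80% claim for this product and state what 48 per group can detect with 80% power at 2-sided 0.05, about 0.50 to 0.51 SD for the mean of three visits or 0.57 SD for a single time point.

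The cost is looking up one file and rewriting one paragraph. Correcting the statement does not in itself require more patients, but the stated power may become less favourable.

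### The sample size assumes a 1-sided 0.05 test but results are judged at 2-sided 0.05, so the stated 80% power is about 70%

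*Protocol article*

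**What the plan says.** Section 2.11 (Estimation of sample size) powers the trial on platelet aggregation rate and states that "A 1-sided 0.05 level of significance and a sample size of 96 participants (48 per group) provided 80% statistical power". The design inputs are given as "autocorrelation coefficient 0.7, 3 time points", and the method as "2-way repeated measures Anova; allocation ration = 1", run in PASS. Recruitment is then raised to 106 (53 per group) for 10% attrition.

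Section 2.13 (Statistical analysis) sets the P value threshold for the analysis: "2- sided 0.05 will be considered as significant". No section provides a one-sided test or exempts the primary outcome from this rule.

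Section 2.13.1 analyses platelet aggregation rate by two-way repeated measures ANOVA and treats a significant group effect as the evidence that the arms differ.

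**The concern.** The level used to size the trial and the level used to judge it differ. A 1-sided 0.05 test has the critical value of a two-sided 0.10 test, so the sizing rests on an easier criterion than the one the data must meet.

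Two things are at stake. First, the 80% is a design property that readers will rely on: a null result could be taken as coming from an adequately powered trial when it was not. Second, two thresholds are in print. A result in the hoped-for direction with a two-sided P value between 0.05 and 0.10 could be called positive by appeal to Section 2.11 and negative by appeal to Section 2.13.

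**Working it through.** **Inputs**
- Planning level 0.05, one-sided; power 80%; 48 per group (Section 2.11).
- Analysis level 0.05, two-sided (Section 2.13).
- Test: group effect in a two-arm ANOVA (Section 2.13.1). It has 1 numerator degree of freedom and 96 − 2 = 94 error degrees of freedom, and F = t², so it is a two-sided t test.

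**The plan's own figure.** The 96 cannot be rebuilt, because the article gives no SD and does not say whether the 14% difference is relative or in percentage points. The check therefore takes the stated 80% at 48 per group as correct and works out what it implies.

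**Step 1. Implied ratio of effect to standard error**

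z(0.95) + z(0.80) = 1.645 + 0.842 = 2.486 (from unrounded values)

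At 48 per group this is a standardized difference of 2.486 / √(48/2) = 0.508. Here the SD is that of whatever summary the group effect compares. The SD, the raw effect, the correlation and the number of time points are all contained in this one ratio and need not be known separately.

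**Step 2. Power under the analysis rule, 48 per group**

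Φ(2.486 − 1.960) = Φ(0.526) = 0.701

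The noncentral t distribution with 94 df gives 0.698.

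**Step 3. Power if all 53 per group supply full data**

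Ratio = 0.508 × √(53/2) = 2.61; Φ(2.61 − 1.96) = 0.743. The noncentral t gives 0.741.

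**Step 4. Sample size for 80% power at 2-sided 0.05**

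48 × (1.960 + 0.842)² / 2.486² = 48 × 1.27 = 60.9, so 61 per group (62 by noncentral t). That is 122 to 124 evaluable. Dividing by 0.90 for attrition gives 136 to 138 recruited.

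| Criterion | Per group | Power (normal) | Power (noncentral t) |
|---|---|---|---|
| 1-sided 0.05 (Section 2.11) | 48 | 80% | 80% |
| 2-sided 0.05 (Section 2.13) | 48 | 70.1% | 69.8% |
| 2-sided 0.05, no dropout | 53 | 74.3% | 74.1% |
| 2-sided 0.05 | 61 (normal), 62 (t) | 80% | 80% |

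The first row is the stated figure, taken as given.

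**The case against.** The strongest reply is that the word 1-sided may be a mislabel. The named method is a repeated measures ANOVA, and an F test uses only its upper tail, which someone could describe as one-sided. If the software was run with the F test at 0.05, power at two-sided 0.05 would be 80%, and only the wording of Section 2.11 would be wrong. Nothing in the text supports this reading, but nothing excludes it either. The missing SD is what would separate the two. Suppose, as an assumption, that 14% means percentage points and that the group effect compares the mean of three time points with correlation 0.7 throughout. The stated 48 per group then implies a per-measurement SD of about 31 on the 1-sided reading and about 27 on the mislabel reading. Section 2.11 needs correcting on either reading.

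A second reply is that the fixed loss of power holds only for a 1-df test. Section 2.11 does not name the ANOVA term that was powered, and a group-by-time test over three time points would have 2 df. That condition is fair, but Section 2.13.1 names the group effect, to which the calculation applies.

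A third reply is that the full analysis set with last observation carried forward could bring the analysed number close to 106. Even with complete data on all 106, power is about 74%, and carried-forward values hold less information than observed ones.

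It is also true that type I error is not inflated if Section 2.13 is followed, since its criterion is the stricter one. The harm is then confined to overstated power.

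**Conclusion.** The concern holds. Sections 2.11 and 2.13 contradict each other on sidedness. As written, the design has about 70% power for its powered outcome at 96 evaluable participants, not 80%: a shortfall of about 10 percentage points, with the type II error half as large again as stated.

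This rests on three conditions: the 80% at 1-sided 0.05 is itself correct, which cannot be verified from the article; the test is the group effect named in Section 2.13.1; and the 1-sided level was the one actually used.

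**What to change.** Keep the 2-sided 0.05 rule of Section 2.13. Check the saved software output for the level and the ANOVA term that were used, then correct Section 2.11:

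- If the output confirms a 1-sided 0.05 level, state that 96 evaluable participants give about 70% power at 2-sided 0.05 for the planned effect.
- If the output shows an F test at 0.05, remove the 1-sided wording and let the 80% stand.

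Give the SD and the unit of the 14% difference in the same place, so that a reader can reproduce the figure. If the primary analysis is later changed, for example to a baseline-adjusted comparison, recompute the power for that test at 2-sided 0.05.

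The cost is a sentence or two in Section 2.11 and, on the text as it stands, a less favourable stated power. No added patients are needed to make the statement true. Restoring 80% would be a separate decision, at about 136 to 138 recruited instead of 106.
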